### Risk factors for musculoskeletal pain and disorders

Some studies show that ergonomic interventions reduce the occurrence of removal for medical leave due to lower levels of exposure to risk factors [22,23]. This study addresses the perception of workers against risk factors that may contribute to the development of musculoskeletal complaints through the Job Factors Questionnaire. This instrument presents a descriptive list of 15 risk factors that should be classified on a scale of zero to ten, indicating how much each factor contributed to the emergence of work-related musculoskeletal symptoms, with zero meaning "no problem" and ten indicating the "largest possible problem" [24].

### Psychosocial factors and fatigue

Data on the perception of workers against psychosocial factors and stress, resulting in fatigue induced by work, will be obtained through the Scale of Need for Recovery [25]. This Likert-type scale has 11 questions and possible answers of numbers up to 4 (0 = never, 1 = sometimes, 2 = often, and 3 = always). The answer “always” indicates an unfavorable situation and receives 3 scores, with the exception of item 4, which features reverse scoring. The total score is obtained by summing the final, transformed by rule of three direct, on a scale of 0 (minimum) to 100 (maximum). In this case, the higher the score, the greater the amount of higher symptoms and need of recovery.

### General health

The WHOQOL-BREF will be used to assess the overall health status and quality of life of workers. This instrument contains 26 questions, divided into four areas: social, psychological, physical, and environment. Each domain consists of questions whose answer scores range between 1 and 5 [26].

### Productivity

Besides this information, other single issues related to productivity at work will be answered by the workers during the follow-ups. Productivity is measured by a single item WHO General Health Questionnaire and Performance at Work [27]. In this, participants should assign a score (0–10) for their labor productivity over the past three months.

### Cost-effectiveness

The cost-effectiveness of interventions will be calculated according to the cost effectiveness incremental [28,29]. For this, we considered the cost required to conduct ergonomic guidelines and cost guidelines in conjunction with job rotation. These values are divided by the time lost from work.

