**Methods/Design:**

A cluster randomized controlled trial will be used to investigate the effectiveness of job rotation to prevent musculoskeletal disorders in industrial workers. The randomized cluster was based in characteristics of production sectors. A total cluster will be 4 sectors, and 957 workers will be recruited from a textile industry and randomly allocated into intervention or control groups. Both groups will receive training on ergonomics guidelines. In addition, the intervention group will perform job rotation, switching between tasks with low, moderate, and high risk for musculoskeletal complaints. The primary outcome will be the number of working hours lost due to sick leave by musculoskeletal injuries recorded in employee administrative data bases. Secondary outcomes measured via survey include: body parts with musculoskeletal pain, the intensity of this pain, physical workload, fatigue, general health status, physical activity level, and work productivity. Secondary outcome measures will be assessed at baseline and after 3, 6, 9, and 12 months. The cost-effectiveness analysis will be performed from the societal and company perspective.

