### Sample size calculation

The number of working hours lost due to sick leave by musculoskeletal injuries (M Group International Classification of Diseases, ICD-10) was used to estimate the sample size. The average time lost during the last three months in companies that the study observed was approximately 1,100 hours. The authors assume that interventions will enable a reduction of this number by 10%, that is, the groups will have a difference of 100 lost working hours, with a standard deviation of 250 hours. A statistical power of 80%, an alpha of 5%, and a possible sample loss of up to 15% is considered. Therefore, 116 participants are needed per group, or 232 in total. But, in this study the calculation of sample size was made by clusters and considered the number of production sectors included. The clusters number was four sectors (n = 957). The intervention group has 504 workers selected from Finishing Socks and Finishing Underwear departments, and the control group is 453selected from Sewing Socks and Sewing Underwear departments (Figure 1).

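### The cost-effectiveness section names an incremental analysis, but the calculation it states divides each programme's cost by time lost, so at equal cost the arm with more sick leave looks better

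*Protocol article*

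**What the plan says.** The Cost-effectiveness section has three sentences.

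- Method: "The cost-effectiveness of interventions will be calculated according to the cost effectiveness incremental".
- Costs: "we considered the cost required to conduct ergonomic guidelines and cost guidelines in conjunction with job rotation".
- Calculation: "These values are divided by the time lost from work".

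The plural subject of the last sentence can only be the two programme costs just named. The section mentions no difference in cost, no difference in hours and no hours averted.

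The direction of the effect measure is fixed elsewhere. The Abstract states: "The primary outcome will be the number of working hours lost due to sick leave by musculoskeletal injuries recorded in employee administrative data bases". Fewer hours are better.

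On perspective, the Abstract says: "The cost-effectiveness analysis will be performed from the societal and company perspective". The Cost-effectiveness section names no cost other than that of delivering the two programmes.

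**The concern.** An incremental cost-effectiveness ratio puts the extra cost of one strategy over the extra benefit it buys. The stated calculation gives instead two separate ratios, one per strategy, each with a harm in the denominator. Such a ratio falls when the harm grows. Someone who followed the sentence as printed would report a figure that penalises rotation for reducing sick leave.

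The economic result would then be uninterpretable, although the Abstract announces it and the Discussion hopes that the trial will inform standards and decisions in occupational health. A smaller matter is that a reader told to expect a societal perspective finds only delivery costs named.

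**Working it through.** **Inputs.** The section gives no figure to reproduce. For scale I take the hours from Sample size calculation: "The average time lost during the last three months in companies that the study observed was approximately 1,100 hours", and "the groups will have a difference of 100 lost working hours, with a standard deviation of 250 hours". This gives T_c = 1,100 h for control and T_i = 1,100 − 100 = 1,000 h for rotation. (An exact 10% cut would be 110 h; I keep the 100 h that the protocol uses.) The protocol does not say what unit the 1,100 h refers to, and the direction of the result does not depend on it. I take time lost to mean the primary-outcome hours. The documents give no programme costs, so all costs below are **assumed** and shown over a range.

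**Step 1: direction of the stated ratio.** With R = C / T, dR/dT = −C / T², which is negative for every C > 0. At a fixed assumed cost of 12,000:

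| Hours lost | 12,000 / hours |
|---|---|
| 800 | 15.0 |
| 1,000 | 12.0 |
| 1,100 | 10.9 |
| 1,300 | 9.2 |

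More sick leave gives a lower, apparently better, figure.

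**Step 2: literal rule against an incremental ratio.** Assumed control cost C_c = 10,000.

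- Literal: C_c / T_c and C_i / T_i.
- Incremental: (C_i − C_c) / (T_c − T_i), with T_c − T_i = 100 h.

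| C_i (assumed) | Literal, control | Literal, rotation | Incremental cost per hour averted |
|---|---|---|---|
| 10,000 | 9.09 | 10.00 | 0 |
| 12,000 | 9.09 | 12.00 | 20 |
| 15,000 | 9.09 | 15.00 | 50 |
| 20,000 | 9.09 | 20.00 | 100 |

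In the first row rotation costs nothing extra and saves 100 hours, yet the literal rule places it behind control.

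**Step 3: how much of the gap is the direction error.** The literal ratio for rotation relative to control is (C_i / C_c) × (T_c / T_i). The second factor is 1,100 / 1,000 = 1.10. The planned benefit therefore adds a 10% penalty to rotation's figure; the rest of the gap is the assumed cost difference.

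**Step 4: when the literal rule would prefer a harmful rotation.** This needs C_i / T_i < C_c / T_c, that is T_i / T_c > C_i / C_c.

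| C_i / C_c (assumed) | Hours lost under rotation must exceed | Rise over 1,100 h |
|---|---|---|
| 1.0 | 1,100 | any rise |
| 1.2 | 1,320 | 20% |
| 1.5 | 1,650 | 50% |
| 2.0 | 2,200 | 100% |

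With hours up by 10%, to 1,210, and C_i = 15,000, rotation scores 15,000 / 1,210 = 12.40, still above control's 9.09.

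**The case against.** The strongest reply is that the section is a three-sentence condensation in loose English. It opens by naming the incremental method with references, and it ties the two costs to that method. On that reading the last sentence is shorthand for a difference in cost over a difference in hours, and the investigators may well intend that. This is a fair reading of intent, so it would be too much to say that the planned analysis is certainly not incremental. But the shorthand is the only calculation stated, and it does not match the method named. This is a formula given wrongly, not a detail left to a fuller document.

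Two stronger readings are tempting, and the documents do not support them.

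- *The rule will rank a harmful programme above a beneficial one.* It can, but only when hours lost rise by a larger proportion than cost. If rotation costs half as much again, the rise must exceed 50%, against a planned change of about 10%. The claim that holds is about direction at equal cost.
- *The plan counts nothing that a societal perspective needs, so that perspective cannot be delivered.* Programme delivery cost is part of a societal analysis. An article may leave its list of cost items to the full protocol. The trial also collects health-professional use (the Nordic questionnaire), self-rated productivity and daily sick-leave records. None of these is a cost, but they show that the claim is not established. What remains is a mismatch in wording between the Abstract and the Cost-effectiveness section.

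**Conclusion.** The point holds in this form: the Cost-effectiveness section names an incremental analysis but states a per-programme ratio of cost to time lost, which takes no differences and rewards more sick leave at equal cost. The direction follows from the algebra and needs no assumption beyond a positive cost. Its size does rest on assumptions: at the protocol's 1,100 h and 1,000 h, the literal rule inflates rotation's figure by a factor of 1.10 on top of whatever the cost ratio is. At equal assumed costs of 10,000 this gives 9.09 for control against 10 for rotation.

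The mismatch between the stated perspectives and the named costs is a secondary and weaker point.

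This should be fixed. It is not critical to the trial: the economic evaluation is not the primary outcome, the effectiveness comparison is untouched, and the correction can be made before analysis.

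**What to change.** Replace the last sentence of the Cost-effectiveness section with an explicit definition:

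ICER = (cost per worker of guidelines plus rotation − cost per worker of guidelines) / (mean hours lost per worker in control − mean hours lost per worker in intervention).

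- **Per worker.** The arms have 504 and 453 workers. Once differences are taken, totals would mix a gap of 504 − 453 = 51 workers into both numerator and denominator.
- **Effect.** Take the denominator from the primary analysis, and report the cost difference and the effect difference beside the ratio.
- **Signs.** If rotation costs more and loses more hours, say that it is dominated; if it costs less and loses fewer, say that it dominates. Do not report a negative ratio as a result.
- **No double counting.** Do not add the wage value of lost hours to this numerator, since the same hours are already in the denominator. If that value is wanted, report it as a separate company net-cost result. The article documents absence records held by Human Resources but no wage data, so their availability would have to be confirmed.
- **Perspective.** Reconcile the Abstract with the section, either by stating the further cost items or by limiting the stated perspective. Either is acceptable.

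The ratio itself costs one sentence and needs no new outcome data or design change. Stating further cost items may mean collecting them; limiting the perspective means giving up the societal claim. I would not present sector-level uncertainty for the ratio as a simple addition: with two sectors per arm, that variance is barely estimable.

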### Statistical analysis

Descriptive statistics (frequencies, means, standard deviation, standard error, confidence interval) will be used in the analysis of socio-demographic characteristics of the population. The Kolmogorov Smirnov test is used to assess the normality of the data. The chi-square test is used to evaluate the blinding of the assessor by comparing the randomization codes and the evaluator. The difference between the groups and their respective confidence intervals are calculated using linear mixed models [30]. The significance level is 5%. The statistical program SPSS will be used for all analyses, which will be held following the principles of intention to treat.

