### Randomization

Randomization was performed at the group level (departments/productive sectors), in order to avoid contamination from workers allocated in the intervention to those in the control group. The productive sectors included in the study were pre-stratified by the level of exposure to risk factors for musculoskeletal pain and disorders. Sectors with similar demands were grouped and randomly divided between intervention and control groups. Using a computer-generated randomization (http://www.randomizer.org) with random numbers to define groups, the randomization was performed by an independent researcher who was not involved in recruitment and assessment. Sealed envelopes will be used. The randomization was performed before baseline measurements.

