### Blinding

Obviously, the nature of the intervention used in this study made it impossible to blind workers and ergonomists. However, the workers’ interview researcher will be blind to the study design and the group assignment. To test blinding, after assessment of outcomes, the worker’s assessment researcher will note his opinion as to the type of intervention received by workers. Moreover, all workers in both groups will receive ergonomic guidelines, used as a placebo intervention.

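### The unadjusted chi-square test of assessor blinding ignores that allocation varies over only four sectors, so its p-value cannot be interpreted; a table of guesses by sector should replace it

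*Protocol article*

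**What the plan says.** The Blinding section of the protocol article keeps the interviewer blind to the study design and to group assignment. As a check, "after assessment of outcomes, the worker’s assessment researcher will note his opinion as to the type of intervention received by workers". It does not say whether that opinion is noted once per worker, per sector or per visit.

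The Statistical analysis section then fixes the test: "The chi-square test is used to evaluate the blinding of the assessor", with the randomization codes set against the evaluator's opinion. The significance level is 5%. The same paragraph names linear mixed models for the differences between groups, but states no allowance for clustering in the blinding test.

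The Randomization section says that allocation was made by department or productive sector, after sectors with similar demands had been grouped. The Sample size calculation section gives four sectors and 957 workers: "The intervention group has 504 workers selected from Finishing Socks and Finishing Underwear departments", and the 453 control workers come from the two Sewing departments.

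**The concern.** A chi-square test assumes independent observations. Here every worker in a sector has the same allocation, and workers in a sector share a department and tasks. An assessor who forms an impression of a sector will tend to repeat it for the workers in that sector. Guesses within a sector are then correlated, while the variable they are compared with takes only four independent values at most. The test treats chance agreement within sectors as strong evidence.

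This is the only check of assessor blinding that the article describes, and the interview-based secondary outcomes lean on that blinding. A spurious significant result could wrongly discredit them.

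**Working it through.** **Inputs.** From the Sample size calculation section: 4 sectors, 504 workers in two intervention sectors, 453 in two control sectors, 504 + 453 = 957, and loss of up to 15%. From the Statistical analysis section: chi-square at 5%. The article gives no ICC for the guesses, no sizes of individual sectors and no number of guesses. ICCs and splits below are assumptions. The only error rate that the plan states for this test is the nominal 5%, and the formula returns it at ICC 0.

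**Case 1: one guess per worker, correlated within sector.** With equal sectors within each arm (about 252 and 226.5 workers), the variance of an arm's proportion is multiplied by 1 + (m − 1) × ICC. The inflation of the variance of the arm difference is

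DE = {[1 + 251 × ICC]/504 + [1 + 225.5 × ICC]/453} / (1/504 + 1/453),

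and the actual two-sided error of the nominal 5% test is 2 × [1 − Φ(1.96/√DE)].

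At ICC 0.01: (3.51/504 + 3.255/453) / (1/504 + 1/453) = 0.014150/0.004192 = 3.376. Then 1.96/√3.376 = 1.067, which gives 28.6%.

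| Assumed ICC | DE | Error, formula | Error, beta-binomial simulation (40,000 runs) |
|---|---|---|---|
| 0 | 1.00 | 5.0% | 4.9% |
| 0.005 | 2.19 | 18.5% | 18.2% |
| 0.01 | 3.38 | 28.6% | 28.5% |
| 0.02 | 5.75 | 41.4% | 41.7% |
| 0.05 | 12.88 | 58.5% | 58.9% |
| 0.10 | 24.76 | 69.4% | 69.7% |

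With 15% loss the formula gives 26% at ICC 0.01, 56% at 0.05 and 67% at 0.10. The rate passes 60% at an ICC of about 0.055 with equal sectors, about 0.047 if sectors split 70/30 within arms, and about 0.064 with equal sectors and 15% loss.

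**Case 2: one random opinion per sector, copied to every worker in it.** There are 2⁴ = 16 equally likely patterns. With sizes 252/252 v 226/227, the test is not significant when the same number of sectors is guessed as intervention in each arm: 1 + 4 + 1 = 6 patterns. The other 10 (62.5%) are significant, 5 in the correct direction and 5 against it. With assumed unequal splits the count is 12 of 16 (280/224 v 250/203, and 300/204 v 280/173) or 14 of 16 (300/204 v 227/226).

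**Direction.** Under the null, significant results fall equally on both sides. Those in the direction of the true allocation are about 14%, 29% and 35% of all trials at ICC 0.01, 0.05 and 0.10, and 5/16 = 31% to 7/16 = 44% in Case 2.

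**Case 3: one opinion recorded per sector.** The table holds four observations. With all four correct, the uncorrected statistic is 4 × (2×2 − 0×0)²/(2×2×2×2) = 4, so p = P(|Z| > 2) = 0.046. The permutation p-value for the same table is 2/6 = 0.33. The chi-square approximation fails here.

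**Can a sector-level test be used instead?** Two of four sectors can be allocated in C(4,2) = 6 ways, so the smallest two-sided permutation p is 2/6 = 0.33. If the sectors were paired before allocation, as the Randomization section may imply, there are 4 ways and the smallest p is 2/4 = 0.50. Neither reaches 5%. A model-based test on four sector proportions would have 4 − 2 = 2 degrees of freedom and would rest on a distributional assumption that four points cannot check.

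**The case against.** The strongest reply is that the size of the inflation is assumed. The article gives neither an ICC nor the recording unit, and a condensed article may leave the unit to the full protocol. This stands. The error rate can only be given as a range starting at 5%, and 957 is an upper limit on the number of workers with a guess. It does not rescue the test, because chi-square is named in the article and is unsuitable under either recording unit unless guesses within a sector are essentially uncorrelated.

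A reader might infer that the test will usually declare blinding broken when the assessor knows nothing. The figures do not support that. Half of the false positives point away from the true allocation, and the share pointing towards it stays below 50% in every scenario above. Nor is a rate above 60% established: it needs an ICC of roughly 0.05 to 0.06, or one opinion per sector.

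A reader might also infer that the blinding check is worthless. It is not. The guess data remain informative as description, and the error under clustering is towards false alarm.

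Finally, one might fault the plan for asking for the opinion only after outcome assessment. That is a trade-off and not an error. The assessor is to be kept blind to the study design, and an earlier question would reveal that different interventions exist.

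The consequence is also limited. The article attaches no decision rule to this test, the primary outcome comes from medical certificates validated by HR, and group differences come from mixed models.

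**Conclusion.** The point holds as a minor one. An unadjusted chi-square test does not keep its 5% level if guesses are recorded per worker and agree within sectors: about 19% at an ICC of 0.005, 29% at 0.01, 59% at 0.05 and 69% at 0.10, and 62.5% if one random opinion is formed per sector of near-equal size. All of these rest on assumed ICCs or sector sizes. If one opinion per sector is recorded, four observations are too few for the test. No permutation test at sector level can reach 5%. The p-value is therefore not interpretable, whichever way it falls.

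Interpretation has a further limit. Arm coincides with department type, Finishing against Sewing, and the opinion follows the outcomes. A correct guess may therefore reflect department, disclosure by the worker or perceived benefit, and not a leak of the allocation. No effectiveness estimate is affected.

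**What to change.** In the Statistical analysis section, replace the chi-square sentence with a plan to tabulate, by sector and without a p-value, the assessor's guesses and the percent correct. In the Blinding section, state the unit in which the opinion is recorded, and add a short field for the reason (for example: worker disclosed it, rotation was seen, perceived benefit, department, no particular reason). Note beside the table that a correct guess does not by itself show that the allocation leaked. Keep the planned timing, after outcome assessment, and do not add an earlier guess.

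The cost is one sentence in the analysis section, a clause on the recording unit and one field on the form. If opinions are taken per worker, that field is completed for up to 957 workers, so a tick-box is preferable to free text.

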### Assessment instruments and outcomes

Although the intervention is applied to the production sectors, the outcomes are on an individual level, since they reflect aspects of the health of workers. Data regarding outcome measures will be assessed at baseline and after 3, 6, and 12 months, except for information relating to removal for sick leave, which will be recorded daily. After a period of 12 months, the sector that had received only ergonomic guidelines will receive job rotation considering the hypothesis of this study in relation to its effectiveness. Both groups of workers will be monitored in a longitudinal study in subsequent months and compared to other workers identified within the criteria for risk analysis for 24 months.

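### Four sectors were randomised, but the stated linear mixed models name no sector effect or small-cluster method; unless inference is at sector level on about 2 df, the 5% level and the intervals will be wrong

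*Protocol article*

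**What the plan says.** Under Randomization, the protocol article states: "Randomization was performed at the group level (departments/productive sectors"). Under Sample size calculation it gives four sectors and 957 workers: 504 in two Finishing departments (intervention) and 453 in two Sewing departments (control). Under Assessment instruments and outcomes it adds: "Although the intervention is applied to the production sectors, the outcomes are on an individual level".

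The sample size assumes that "the groups will have a difference of 100 lost working hours, with a standard deviation of 250 hours". It continues: "A statistical power of 80%, an alpha of 5%, and a possible sample loss of up to 15% is considered". The result is 116 per group. The text then says that the calculation was made by clusters, but gives no ICC and no design effect.

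Under Statistical analysis, the comparison of arms is one sentence: "The difference between the groups and their respective confidence intervals are calculated using linear mixed models". The level is 5%, the software is SPSS and the principle is intention to treat. No random effect, degrees-of-freedom method or covariate is named.

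**The concern.** When whole sectors are randomised, the sectors carry the evidence about the intervention. Workers in one sector share tasks, supervision and pace, so their sick leave is likely to be correlated. Adding workers to a sector does not replace adding sectors. With two sectors per arm, only 4 − 2 = 2 degrees of freedom are left to estimate the between-sector variation that the comparison of arms has to be judged against.

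The name of the model does not settle this. Workers are also assessed repeatedly, which is a sufficient reason to choose a mixed model with a worker effect and no sector effect. The only worked calculation in the article treats workers as independent. If the analysis does the same, the interval is too narrow and a null intervention can easily be declared effective. Adding a sector random intercept is not enough by itself: with four clusters its variance is often estimated as zero, and the test then falls back to a worker-level one.

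**Working it through.** **Inputs from the article.** Difference 100 h, SD 250 h (taken as between workers, as the plan's formula does), power 80%, alpha 5% (two-sided reproduces the figure), loss 15%; four sectors; 504 and 453 workers, so a mean of 957/4 = 239.25 per sector.

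**Assumed.** The ICC, shown from 0.005 to 0.05 because the article gives none; equal sector sizes in the design effect and the simulation.

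**The plan's own figure.** n per group = 2 × [250 × (1.96 + 0.842)/100]² = 98.1. Allowing for loss, 98.1/0.85 = 115.4, so 116. The stated figure is reproduced, with no clustering allowance in it.

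**Sector ignored.** DEFF = 1 + (239.25 − 1) × ICC. True level = 2 × [1 − Φ(1.96/√DEFF)]. At ICC 0.01: DEFF = 3.38, 1.96/1.839 = 1.066, level 29%.

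**Sector random intercept.** Simulated with four clusters of 239 and no intervention effect, the sector variance being truncated at zero as in REML. Three references were used: normal (1.96); Satterthwaite-type (2 df when the variance is positive, worker-level otherwise); and 2 df always (critical value 4.30). A plain t-test on the four sector means with 2 df was run alongside.

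| Assumed ICC | Sector ignored | Random intercept, normal | Random intercept, Satterthwaite-type | Random intercept, df fixed at 2 | Sector means, t on 2 df |
|---|---|---|---|---|---|
| 0.005 | 18.5% | 10% | 6.8% | 0.2% | 5% |
| 0.01 | 29% | 13% | 7.5% | 0.7% | 5% |
| 0.02 | 41% | 16% | 7.2% | 1.7% | 5% |
| 0.05 | 59% | 18% | 6.0% | 3.5% | 5% |

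The sector variance is estimated as zero in about 37% of trials at ICC 0.005 and 25% at 0.01. That is why the Satterthwaite-type test stays above 5%. It also explains why fixing the df at 2 in the mixed model errs on the cautious side: at the boundary, the worker-level standard error is paired with the larger critical value. The normal-reference column tends to P(|t₂| > 1.96) = 18.9%.

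**Interval and power.** SE = 250 × √[DEFF × (1/504 + 1/453)]. With DEFF = 1, SE = 16.2 h and the half-width is 1.96 × 16.2 = 32 h. At ICC 0.01, SE = 29.8 h and the half-width on 2 df is 4.30 × 29.8 = 128 h. Power for 100 h comes from the noncentral t on 2 df.

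| Assumed ICC | 95% half-width, 2 df | Power for 100 h, 2 df |
|---|---|---|
| 0.005 | 103 h | 59% |
| 0.01 | 128 h | 45% |
| 0.02 | 167 h | 31% |
| 0.05 | 250 h | 18% |

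With sector ignored, the half-width is 32 h whatever the ICC. An observed difference of 100 h would therefore look decisive under one analysis and inconclusive under the other at every ICC in the table.

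**The case against.** The strongest reply is that the text is silent, not wrong. A linear mixed model can carry a sector effect, and an article may leave random effects, df method and covariates to a fuller plan. This stands to the extent that a reader might infer that the analysis has no sector term and no small-cluster correction; the article does not say so. The 18.5% to 59% figures therefore apply only if sector is left out. The reply does not dispose of the point, because the ordinary way of including sector also misses 5% with four clusters, and nothing in the article makes sector the unit of inference.

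Second, with Satterthwaite-type df the excess is modest, and every ICC is assumed. Both are true. At an ICC of zero there would be no inflation, but the design gives no ground for assuming zero.

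Third, a reader might infer that leaving out pre-trial sick leave also invalidates the test. It does not: under randomisation it costs precision and leaves chance imbalance between sectors uncorrected, but the 5% level is unaffected. Nor does the article show that worker-level records from before randomisation were used. It gives one average over three months and does not name its source there.

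Fourth, the sentence "The Kolmogorov Smirnov test is used to assess the normality of the data" has no stated consequence, and the article gives no distribution for hours lost or time at risk. These are minor and do not support a claim about the level.

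Finally, sector-level inference cannot rescue the design. That is correct. It is a reason to report an honest interval and not a reason to report a narrow one.

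**Conclusion.** The concern holds in conditional form. Four sectors were randomised, and the stated analysis does not tie inference to them. Unless it rests on about 2 df at sector level, the nominal 5% and the 95% intervals will be wrong. For assumed ICCs of 0.005 to 0.05, the true level is about 18.5% to 59% with sector ignored, 10% to 18% with a random intercept and normal reference, and 6% to 7.5% with Satterthwaite-type df. These figures rest on normally distributed sector effects, similar sector sizes and the assumed ICCs. The first range is not a statement about what the investigators will do, since a sector term is not excluded. The point bears on the validity of the primary result and should be settled before analysis.

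**What to change.** In Statistical analysis, name sector as the unit of inference for the primary and secondary outcomes, in one of two ways:

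- Compare the four sector means, or the sector means of worker-level residuals from a covariate model without the intervention term, between arms with a t-test on 2 df. This held 5% at every ICC tried.
- Fit a mixed model with a sector random intercept and denominator df fixed at 2. This is conservative when the ICC is small.

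Report the corresponding interval as the main result. Adjust each survey outcome for its baseline value. If worker-level records exist, adjust sick leave for hours lost before randomisation. Describe both adjustments as a gain in precision only.

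The change is a matter of wording, plus one data extract if earlier sick-leave records are used. The real cost is precision: at SD 250 and ICC 0.01, before any covariate adjustment, the half-width is about 128 h instead of 32 h, and power for 100 h is about 45% against the 80% planned. The report should say this openly.

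It should also say that both intervention sectors are Finishing and both control sectors are Sewing, so no analysis of these four sectors can separate job rotation from the type of work. That limits the conclusion whichever model is used.
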